### Interventions

#### Control group

Participants in control group practices received a printed copy of the summary version of the guideline and a written reminder of how to access it [11]. For some practitioners, this provides an additional exposure to the CPG that was originally disseminated by the NHMRC in 2004.

#### Intervention group

Intervention group practitioners received a theory-based implementation intervention developed to address the hypothesised determinants of CPG implementation identified in phase one of this project. In phase one, semi-structured interviews, underpinned by a theoretical domains framework [56], were conducted with physiotherapists and chiropractors in Victoria, Australia. Thematic analysis was used to map the identified barriers and facilitators of the target behaviours to the theoretical domains framework. The most salient domains identified formed the basis of a survey, which was distributed to a random sample of practising physiotherapists and chiropractors in Victoria, South Australia, and Western Australia. The survey quantified the association between constructs from these domains and intention to practice in a manner consistent with the guideline recommendations. Both the findings of interviews and survey informed the design of the intervention, and will be published elsewhere.

The intervention consisted of: a full-day symposium-style event involving a combination of didactic lectures delivered by peer opinion leaders (identified in consultation with representatives from the physiotherapy and chiropractic associations), small group discussion led by trained clinical facilitators, and practical sessions; supporting written material; and a follow-up phone call. Separate symposia were held for physiotherapists and chiropractors. All practitioners in the intervention group, including those who were not able to attend the symposium, received a DVD including videos of the didactic sessions and printed resources about LBP management. A clinical member of the project team attempted to follow-up all practitioners with a telephone call to discuss difficulties encountered in implementing behaviours and strategies to overcome these. More detail on the intervention, including the development process, will be reported in a separate publication. Symposia details are available in Additional File 1 - 'ALIGN intervention content.'

Finally, while not formally a component of the intervention or control group, the practitioner data collection procedure involves completion of patient checklists about LBP management and may act as a prompt to change practitioner behaviour. The checklist includes a broad range of diagnostic procedures and interventions potentially used for patients with acute non-specific LBP, irrespective of supporting evidence.

#### Timing of recruitment, intervention delivery, and follow-up

The physiotherapist and chiropractic symposia took place on 20 and 27 February 2010, respectively. Practitioners in the intervention group were mailed a DVD of material from the symposium for their professional group on 29 March 2010. Practitioners in the intervention group received a follow-up phone call two to four weeks after either attending the symposium or being sent the DVD. Materials were sent to the control group on 10 March 2010.

Patient participant recruitment will take place over a five-week period, beginning at least three months post-symposium delivery (31 May 2010). Each practice will recruit patients for a period of two weeks (a longer period was judged to place too great a burden on practitioners). Practices will be randomly allocated to recruit patients in either the first (31 May to 11 June 2010) or second (21 June to 2 July 2010) data collection period. Practitioners who are not able to collect data in either of these periods (*e.g*., on holiday), will be invited to select an alternative fortnight of data collection between July and September 2010.

Figure 1 details the timing of recruitment, intervention delivery, and data collection periods for practitioner and patient participants.

**Figure 1 F1:**
[figure not shown]
**Timing of recruitment, intervention delivery, follow-up of practitioner, and patient participants**.

#### Intervention fidelity

We will evaluate intervention fidelity, which is the extent to which the intervention, as delivered, was adhered to as planned [57]. The proportion of practitioners in the intervention group who attended the symposium, received the follow-up call, and viewed the DVD has been documented. The symposia were audio- and video-recorded and will be transcribed verbatim. Observed adherence will be assessed by content analysis of the symposium transcripts to evaluate which intervention sections were covered, and which behaviour change techniques were delivered. An independent assessor attended each symposium and completed a checklist to indicate whether or not planned intervention components and behaviour change techniques were used. We will report the proportion of practitioners who received each different component of the intervention and the data from the checklist completed by the independent assessor in the main trial publication; the remaining components of this evaluation will be reported in a separate publication.

### Study outcomes

#### Primary outcomes

The primary outcome at the practitioner level is whether the practitioner orders, undertakes, or recommends a lumbar x-ray for the acute non-specific LBP patient over the two-week data collection period (occurring three months post-symposium). The primary outcome at the patient level is LBP specific disability three months post-onset of their acute LBP episode (Table 1).

**Table 1 T1:** Outcome measures

Outcome *(outcome category)*	Data collection method	Outcome assessment period	Source	Level data collected at
**Inference intended at the practitioner level**				
X-ray referral *(practitioner behaviour)*^1^	Checklist completed by practitioner	3 to 4 months post-symposium	Practitioner	Patient
Advice to stay active *(practitioner behaviour)*	Checklist completed by practitioner	3 to 4 months post-symposium	Practitioner	Patient
Imaging referral excluding x-ray *(practitioner behaviour)*	Checklist completed by practitioner	3 to 4 months post-symposium	Practitioner	Patient
Advised bed rest *(practitioner behaviour)*	Checklist completed by practitioner	3 to 4 months post-symposium	Practitioner	Patient
X-ray referral (file audit) *(practitioner behaviour)*	Clinical file audit	0 to 7 months post-symposium	Practitioner case notes	Patient
Imaging referral excluding x-ray (file audit) *(practitioner behaviour)*	Clinical file audit	0 to 7 months post-symposium	Practitioner case notes	Patient
Intention to adhere to CPG recommendations:	Questionnaire	Baseline, 4 months post-symposium	Practitioner	Practitioner
X-ray referral				
Imaging referral excluding x-ray				
Advice to stay active				
Bed rest advice				
*(predictor practitioner behaviour)*				
Behavioural constructs^2 ^(e.g., knowledge, beliefs about capabilities) *(predictor practitioner behaviour)*	Questionnaire	Baseline, 4 months post-symposium	Practitioner	Practitioner

**Inference intended at the patient level**				
LBP specific disability^1^ *(health outcome)*	Questionnaire	3 months post-onset acute LBP episode	Patient	Patient
Pain severity *(health outcome)*	Questionnaire	3 months post-onset acute LBP episode	Patient	Patient
X-ray occurred *(health behaviour)*	Questionnaire	3 months post-onset acute LBP episode	Patient	Patient
Fear-avoidance beliefs *(predictor health behaviour)*	Questionnaire	3 months post-onset acute LBP episode	Patient	Patient
Health-related Quality of Life *(health outcome)*	Questionnaire	3 months post-onset acute LBP episode	Patient	Patient
Health Service Utilisation and Productivity Gains/Losses	Questionnaire	3 months post-onset acute LBP episode	Patient	Patient

Table adapted from McKenzie *et al*. [33]. See Additional File 2 - 'ALIGN outcome definitions' for details of outcome definitions.

^1^Primary outcome. ^2^Table 2 provides details of the behavioural construct domains.

The rationale for selecting these outcomes as primary outcomes is fully described in McKenzie *et al*. [33]. In brief, the intervention focused on two key recommendations from the CPG: diagnostic plain x-rays of the lumbar spine are rarely necessary in the management of acute LBP, and patients should be advised to remain active. The primary outcome at the practitioner level measures the effectiveness of the intervention in changing the practitioners' behaviour for the first recommendation, x-ray referral. The primary outcome at the patient level measures the effectiveness of the intervention in changing the practitioners' behaviour for the second recommendation, providing advice to stay active, and assessing whether this change results in improvements for the patients in terms of short-term disability.

#### Secondary outcomes

Secondary outcomes include measures of practitioner behaviour (provided advice to stay active, advised bed rest, referred for imaging excluding x-ray), predictors of practitioner behaviour (practitioner intention to behave in a manner consistent with the CPG's recommendations, behavioural constructs), patient health outcomes (pain severity, HRQoL), a predictor of patient health behaviour (FAB), and a patient health behaviour (x-ray-occurred). The outcomes, data collection methods, and assessment periods are included in Tables 1 and 2. Justification for the inclusion of these outcomes follows.

**Table 2 T2:** Behavioural construct domains

		Domain measured for behaviour	
		
Domains	Explanation	**X-ray referral**^**1**^	Advice to stay **active**^**2**^
**Behavioural intention**			
Intention	The extent to which the practitioner intends to perform the behaviour.	✓	✓
**Other behavioural domains**			
Beliefs about capabilities	The extent to which the practitioner feels confident in/control over performing the behaviour.	✓	✓
Beliefs about consequences	The extent to which the practitioner is in favour of performing the behaviour and has positive behavioural beliefs.	✓	✓^3^
Knowledge	Whether the practitioner has knowledge of the behaviour.	✓	✓
Professional role and identity	The extent to which the practitioner feels it is their professional responsibility to perform the behaviour.	✓	✓
Social influences	The extent to which the practitioner feels social pressure to engage in the behaviour.	✓	✓
Environmental context and resources	The extent to which the practitioner feels the environmental context supports performance of the behaviour.	✓	✓
Memory	The extent to which the practitioner remembers to perform the behaviour.	✗	✓

^1^Managing patients without referral for plain x-ray.

^2^Advising patients to stay active.

^3^Includes measurement of practitioners' fear-avoidance beliefs about physical activity and pain.

##### Practitioner behaviour

The outcome 'imaging referral excluding x-ray' has been included to estimate the effect of the intervention on practitioners' referral for other types of imaging. Including this outcome stems from a concern that while practitioners may reduce their use of x-rays, they may concurrently increase their use of other forms of imaging. Other forms of imaging are rarely recommended for acute LBP [11]. The outcomes 'advice to stay active' and 'advised bed rest' have been included as additional measures to assess the effectiveness of the intervention in changing practitioners' behaviour, with advice to stay active recommended, and advising bed rest not recommended. These outcomes are predicted to mediate the relationship between the intervention and patient LBP specific disability.

##### Predictors of practitioner behaviour

We have included measures of behavioural intention and other behavioural constructs (such as knowledge and beliefs about capabilities) as predictors of behaviour. Several outcomes measuring practitioners' intentions toward behaving in a manner consistent with the CPG's two recommendations are included because intention has been shown to be predictive of behaviour [58]. Intention is considered separately from the other behavioural constructs because it is thought to mediate the relationship between these constructs and actual behaviour. Details of the other behavioural constructs are reported in Additional File 2 - 'ALIGN outcome definitions' and Additional File 3 - 'ALIGN data collection instruments.'

##### Patient health outcomes

We have included pain severity as an additional measure of the effectiveness of the intervention on patient level health outcomes because pain severity is a recommended core outcome measure in LBP research [59]. In addition, it is useful to examine if the small benefits on pain observed in patient randomised trials, which underpinned the guidelines, are observed in a pragmatic setting with a less intensive patient level intervention.

We have included a preference-based measure of HRQoL in the set of patient-level outcomes to facilitate estimation of intervention effects in terms of quality adjusted life-years (QALYs). QALYs are commonly used in healthcare priority setting to compare interventions over multiple dimensions of HRQoL (in this case pain, pain-related disability, and physical function *inter alia*). Measurement of QALYs will permit the results of cost-effectiveness analyses to be expressed in terms of incremental cost per QALY.

##### Predictor of patient health behaviour

Fear-avoidance beliefs, measured at the patient level, will be included as a potential predictor of patient health behaviour. A recent systematic review investigating factors that were predictive of disability up to three months after the index consultation, identified a range of psychosocial factors, including depression, job physical demands, and FABs [60]. Fear-avoidance beliefs were more frequently shown to be associated with acute LBP compared with other psychosocial factors, and has been included for this reason.

##### Patient health behaviour

Patients will be asked if they received an x-ray. When patients do not receive either a referral for an x-ray or an x-ray from their practitioner, they may choose to see another practitioner who may provide an x-ray referral. While evidence of effectiveness of the intervention in changing x-ray referral rates by practitioners may be observed, it is of interest to examine if this ultimately changes the proportion of patients who receive an x-ray.

### Outcome measurement

Practitioner behaviour will be measured through practitioner-completed checklists of patient consultations and through clinical file audit. Practitioners will complete a checklist for each patient consultation over the two-week data collection period, indicating diagnostic procedures and interventions ordered, undertaken, or recommended. Outcomes measured through the checklists represent the practitioners' self-reported behaviour approximately three to four months post-symposium delivery. Clinical file audit will be undertaken for consenting patients. Outcomes measured through clinical file audit will represent practitioners' behaviour over the period zero to approximately seven months post-symposium delivery. The practitioner checklist and details of the data to be extracted from clinical file audit are available in Additional File 3.

Predictors of practitioner behaviour will be measured through a questionnaire, administered as a paper-based questionnaire or through the internet, at baseline and approximately four months following symposium delivery.

Patient health outcomes, patient health behaviour, and predictor of patient health behaviour, will be measured through a questionnaire, administered as a paper-based questionnaire or through the internet, at three months post-onset of their acute LBP episode. The patient questionnaire is available in Additional File 3.

Details of the outcome definitions are available in Additional File 2.

### Data quality assurance

Completed practitioner and patient questionnaires will be checked for errors and missing data as they are returned, and participants will be followed up to clarify anomalies. Double data entry will be used for paper-based questionnaires, and practitioner- and patient-completed checklists. When inconsistencies are found, these will be corrected by referring back to the paper-based version. Practitioner-completed checklists will be checked, as they are returned, to determine if there are items or sections that have consistent errors or missing data. When this occurs, practitioners will be followed up to discuss any misunderstandings in completing the checklists. Patient participants who have consented to follow-up data collection will be contacted if there is missing data on their patient completed checklist. Practitioners of these patient participants will be contacted if there is missing data on the practitioner-completed checklist. Processes will be put in place to monitor the number of practitioner- and patient-completed checklists received each day over the data collection period. A continuous sampling plan will be used to check a sample of data extracted from patient clinical files [61,62].

### Sample size

The primary practitioner outcome is x-ray referral. In our original sample size calculation for this outcome, we estimated that we would require 136 practices (68 physiotherapy and 68 chiropractic practices), each completing checklists for an average of 20 patient participants (providing a total of 2,720 patient participants), to provide 80% power to detect a difference of 10% in x-ray referral between intervention groups. This assumed a 39% x-ray referral rate in the control group, a 5% significance level, and an ICC of 0.10, and allowed for 20% attrition in practices. Empirical research has suggested ICCs of the order of 0.10 for process variables, such as x-ray referral, in primary care [63]. Data on x-ray referral rates were not available for the Australian context, so the x-ray referral rate of 39% was estimated from international research and assumptions regarding the process of x-ray referral in Australia. More specifically, for chiropractors, several international studies have estimated that referral for x-ray for acute LBP ranges from 62% to 72% [17,20,23]. For physiotherapists, we assumed that x-ray referral rates would be similar to those found in Australian general practice, which has been estimated at 28% [64], because many physiotherapists treat patients with LBP on referral from, and in conjunction with, GPs. Because we intended to recruit an equal number of patient participants from physiotherapy and chiropractic practices, we estimated the pooled x-ray referral rate to be 47%. Interventions comparing standard CPG dissemination with no intervention control groups have shown improvements in care of approximately 8% [4]. We therefore anticipated a decrease in the percentage of x-ray referral in the control group of this magnitude, providing an estimated referral rate of 39%.

As previously mentioned, we received a better than expected response from practices wishing to participate (133 physiotherapy and 77 chiropractic practices), and made a decision to include all practices because of uncertainties in the sample size calculation, including our estimate of ICC, the average number of patient participants for whom checklists are completed per practice (cluster size), variation in the cluster size, and the estimated x-ray referral rates. Assuming 168 practices complete the data collection (allowing for 20% attrition), we have investigated the likely width of the 95% CI for the risk difference and the log odds ratio for the primary practitioner outcome x-ray referral, assuming a range of values of the sample size parameters (Additional File 4 - 'ALIGN sample size calculations'). From this investigation, the width of the 95% CI for the observed difference in x-ray referral rates between groups is likely to be in the range of ±5% to ±7%. On the log odds scale, this is equivalent to a range of ±0.26 to ±0.41.

### Effectiveness analyses

#### Analysis subsets

The principle of intention-to-treat (ITT) is generally the recommended analysis approach for randomised trials because it maintains the comparability of the intervention groups, in known and unknown prognostic factors, brought about through randomisation, thus providing an unbiased estimate of intervention effect. In addition, non-compliance by practitioners and patients is allowed for, therefore providing an estimate of intervention effect that is more reflective of actual clinical practice [65,66]. For this reason, ITT analysis has been suggested for pragmatic trials [67].

In patient randomised trials, requirements of an ideal ITT analysis include compliance with the randomised intervention, no missing responses, and follow-up on all participants [65]. In a CRT, definition and application of an ITT analysis is more challenging [68] because of complexities with the hierarchical structure of the design and recruitment of participants potentially occurring post-randomisation of the clusters. More specifically, in a CRT such as ours, practices, practitioners, and patients may withdraw, or be lost to follow-up. In addition, during the recruitment phase of patient participants, practitioners may not actively recruit patients, potentially leading to empty clusters (this may be differential by group); they may recruit a differential number of participants depending on allocation status; or they may selectively recruit patients (leading to patients with different characteristics between groups) [68]. Statistical methods for handling missing data and dealing with selection bias in CRTs are limited [69], and for some forms of missing data (empty clusters), there is currently no statistical solution [68].

We therefore plan to present a modified ITT analysis as our primary analysis, where we will analyse clusters and participants (practitioners and patients) as they have been randomised, regardless of the intervention they have received, but will not impute missing data. As part of the secondary analyses, we plan to identify potential predictors of missing data through modelling, and include these predictors in the primary analysis model. Where possible, we plan to collect information on reasons for practice, practitioner, and patient withdrawal. To investigate potential selective recruitment, we will compare the practice list sizes [45], numbers of recruited participants, and their characteristics, between groups (examples of this include [70,71]).

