The patient recruitment process has the potential to introduce selection bias because patients are recruited post-randomisation, and this is undertaken by practitioners who are aware of their own allocation status [51]. In cluster trials such as ALIGN, which include patients with an acute condition, it is generally not possible to recruit patient participants prior to randomisation of practices [45]. Potential strategies for minimising selection bias occurring through patient recruitment in ALIGN included (i) researchers blinded to group allocation recruiting in practices, (ii) reception staff recruiting patients, (iii) researchers blinded to group allocation searching clinical files without patient consent, (iv) using de-identified data produced by software for trawling electronic clinical files, and (v) using administrative data. It was not possible for us to implement any of these options. We did not have the resources available to place recruiters at each of the practices (option (i)). Some practices did not have reception staff, precluding the use of option (ii). Australia's state and commonwealth privacy legislation does not allow researchers to access clinical files without patient consent (option (iii)) [52]. Most physiotherapy and chiropractic practices do not use electronic clinical files, precluding the use of option (iv). Finally, unlike in the general practice setting where administrative data on x-ray referral is available (MediCare Australia), this data is not available for physiotherapists and chiropractors. Given these limitations, we plan to report data to assess potential selection bias. Details are available in sections 'Analysis subsets' and 'Descriptive analyses at baseline.'

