#### Primary analyses

We will estimate the effectiveness of the intervention on primary and secondary outcomes with marginal modelling using generalised estimating equations (GEEs). These models will appropriately account for correlation of responses within practice. We plan to fit an exchangeable correlation structure, where responses from the same practice are assumed to be equally correlated [50,72]. Additionally, we intend to use robust variance estimation that will provide valid standard errors even if the within-cluster correlation structure has been incorrectly specified [73,74]. For binary outcomes, a logit link function will be used. In the event that the ICC of an outcome for a particular analysis is negative, we will fit a generalised linear model with no adjustment for clustering (*e.g*., ordinary linear regression), making the assumption that in the context of cluster-based evaluations, negative ICCs are more likely to occur through sampling error than because of a true negative ICC [50].

Our primary analyses of outcomes will include adjustment for stratification variables (professional group and location of the practice) and pre-specified potential confounding variables (Figure 2). The potential confounders have been selected through discussion amongst the investigators and from published research (see Figure 2 notes). All pre-specified confounders will be included in the models even when no baseline imbalance exists. We have chosen this approach because confounder selection strategies that are based on collected data, (*e.g*., selecting confounders using preliminary statistical tests) result in models with poor statistical properties, such as incorrect type I error rates [75-78]. In the circumstance that there is limited data or events (*e.g*., advised bed rest), or both, to adjust for all confounders, we will report estimates of intervention effect from models including only the stratification variables, and baseline of the outcome variables where appropriate (FAB, intention, and behavioural constructs).

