#### Secondary analyses

We will conduct a subgroup analysis to examine whether the effect of the intervention on x-ray referral is modified by professional group (physiotherapist versus chiropractor). We hypothesise that the effect of the intervention may differ by professional group because x-rays are seen as more integral to the treatment of patients for chiropractors compared with physiotherapists [22]. We will examine this by fitting a model that includes an interaction term between intervention group and professional group. The estimated ratio of odds ratios and its 95% CI will be presented from this model.

GEEs will yield unbiased estimates of intervention effect only when data are missing completely at random, or when known covariates that are associated with the missing data mechanism are included in the model (missing at random) [69]. As part of the secondary analyses, we plan to identify potential predictors of missing data through modelling (*e.g*., [81]), and include these predictors in the primary analysis model. We will investigate methods to impute missing outcome data collected at baseline (*e.g*., baseline behavioural constructs, FAB) [82]. Finally, we will investigate methods to adjust for potential differential recruitment [68].

A disadvantage of using GEEs is that only one level of clustering can be modelled. For data collected at the patient level, there are three levels of data: practices, practitioners, and patients. It is possible to allow for clustering at the practice level or the practitioner level. While we have chosen to adjust for clustering at the practice level, because this is the unit of randomisation, there may be an argument for adjusting at the practitioner level if the variation at this level is larger; this could be predicted to arise because the practitioner has a more direct influence on patient outcomes (such as x-ray referral). We will therefore undertake sensitivity analyses investigating the impact of allowing for clustering at the level of the practitioner.

We plan to undertake explanatory analyses to investigate if intervention effects are mediated by our hypothesised predictors of practitioner behaviour [83-85]. Detailed description of our theoretical model and results of these explanatory analyses will form separate publications.

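### The secondary missing-data analysis may adjust for variables that the intervention itself changes, and the primary model loses patients whose outcome is recorded but who lack a covariate

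*Protocol article*

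**What the plan says.** All statements are in the protocol article.

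- **Missing data, primary analysis (Analysis subsets).** Clusters and participants are analysed as randomised, "regardless of the intervention they have received, but will not impute missing data".
- **Covariates, primary analysis (Primary analyses).** "All pre-specified confounders will be included in the models even when no baseline imbalance exists". The one relief is for limited data or events, where "we will report estimates of intervention effect from models including only the stratification variables", plus the baseline value of the outcome where there is one.
- **Missing data, secondary analysis (Analysis subsets, repeated in Secondary analyses).** "we plan to identify potential predictors of missing data through modelling, and include these predictors in the primary analysis model". The reason given is that GEE estimates remain unbiased under missing at random once covariates linked to the missingness are in the model.
- **Baseline data (Secondary analyses).** "We will investigate methods to impute missing outcome data collected at baseline", with behavioural constructs and fear-avoidance beliefs as examples.
- **Timing (Recruitment of patient participants).** "patients are recruited post-randomisation, and this is undertaken by practitioners who are aware of their own allocation status".
- **Advice to stay active and bed-rest advice (Practitioner behaviour, under Secondary outcomes).** "These outcomes are predicted to mediate the relationship between the intervention and patient LBP specific disability".

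**The concern.** Two separate weaknesses follow from these rules.

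**Predictors of missingness used as covariates.** Patients enter the trial after the intervention has been delivered. Apart from demographics, most of what is known about a patient who does not return the three-month questionnaire comes from visit records that the intervention may have influenced. The practitioner checklist holds advice to stay active and bed-rest advice. If one of these predicts non-response and is entered in the outcome model, the arm coefficient no longer estimates the total effect of the intervention. The section on primary outcomes says the disability outcome is meant to show whether changed advice benefits patients, so that is the effect that would be removed. An analysis meant to check the disability result against attrition could then mislead more than the attrition does.

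**Covariates that are themselves missing.** With every confounder compulsory and nothing imputed, a standard GEE fit uses only records complete on all covariates. A patient with a recorded x-ray decision is lost if, for example, the practitioner left a baseline item blank. What is then analysed is narrower than everyone with an observed outcome, and the patients left out may differ between arms.

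**Working it through.** **1. The plan's own figure.** The Sample size section gives 136 practices. Inputs there: 39% control rate, 10-point difference, 80% power, 5% significance, ICC 0.10, 20 patients per practice, 20% attrition. For 39% v 29% with a continuity correction, 371 patients per arm are needed. The design effect is 1 + 19 × 0.10 = 2.9. Then 371 × 2.9 = 1,075.9 per arm; 1,075.9 / 20 = 53.8 practices; 53.8 / 0.80 = 67.2, rounded up to 68 per arm, or 136. This agrees. The point does not turn on this figure, but the same inputs serve in step 4.

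**2. Adding a mediator as a covariate.** The documents give no effect of advice on disability and no response rates, so these inputs are assumptions: total effect −1.0 point; advice given to 50% of control and 70% of intervention patients; about 59% response, depending on advice and one baseline covariate; linear model, no clustering; 2,000,000 simulated patients per scenario.

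The arm coefficient after adjusting for advice is

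total effect − (difference in advice × effect of advice).

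- All mediated: effect of advice = −1.0 / 0.20 = −5.0, so −1.0 − 0.20 × (−5.0) = 0.
- Half mediated: effect of advice = −2.5, so −1.0 − 0.20 × (−2.5) = −0.5.
- None mediated: −1.0 − 0 = −1.0.

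The simulation, with outcomes missing, gave:

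| Share mediated by advice | Complete cases, baseline covariate only | Advice added as covariate | Advice used only as imputation auxiliary |
|---|---|---|---|
| All | −0.89 | 0.00 | −1.00 |
| Half | −0.95 | −0.50 | −1.01 |
| None | −1.01 | −1.01 | −1.01 |

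Attrition alone moved the estimate by at most 0.11. Adding the mediator moved it by 0.5 to 1.0 when mediation was present.

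**3. Practices that depend on one practitioner.** From Recruitment of physiotherapy and chiropractic practices: 133 + 77 = 210 practices and 180 + 88 = 268 practitioners. Each practice has at least one consenting practitioner, which leaves 268 − 210 = 58 others. At most 58 practices can therefore have more than one, so at least 210 − 58 = 152 (72%) have exactly one. In these, one missing practitioner-level covariate removes every patient in the practice. The notes to Figure 2 name the practitioner questionnaire as one source of covariates.

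**4. Cost in precision.** Take 210 × 0.80 = 168 practices (84 per arm), 20 patients each, ICC 0.10, 39% v 29%. The effective number per arm is 84 × 20 / 2.9 = 579. The 95% CI half-width is 1.96 × √[(0.39 × 0.61 + 0.29 × 0.71) / 579] = 5.4 points. The share of practices lost is assumed, as no rate is given:

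| Whole practices lost | Half-width (points) | Power |
|---|---|---|
| 0% | 5.4 | 95% |
| 10% | 5.7 | 93% |
| 20% | 6.1 | 90% |
| 30% | 6.5 | 85% |

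If the same shares of patients are lost evenly within practices, the half-widths at 10%, 20% and 30% are 5.5, 5.6 and 5.8 points. All values lie within the ±5% to ±7% that the protocol expects, so selection matters more here than precision.

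**The case against.** **The protocol names no predictors.** A reader might infer that the plan does condition on mediators. The text does not support that: it leaves the predictors open, and professional group, location and baseline questionnaire items are equally available. For pre-randomisation predictors the criticism falls away. What stands is that nothing excludes the advice variables. Nor can every patient variable be a candidate: Table 1 collects patients' fear-avoidance beliefs on the same three-month questionnaire as disability, so they cannot predict its non-return.

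**It is only a secondary analysis.** Correct. A reader might infer that the primary disability estimate is biased by this step; it is not touched. The harm is to the reassurance the secondary result is meant to give.

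**The illustration is built to show harm.** Partly fair. The full-mediation case must give zero by construction, and a 5-point effect of advice has no support in the protocol, which speaks of small benefits on pain. Hence the range down to no mediation, where there is no harm.

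**Data-driven selection.** The Primary analyses section rejects choosing confounders from the data, and the secondary analysis selects covariates that way. A reader might call this a contradiction. It is a tension only, because the primary model stays pre-specified.

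**Missing baseline data are already addressed.** In part. Imputation will be investigated, but only as a secondary analysis and only for outcome data collected at baseline. Returned questionnaires are also checked and anomalies followed up, which should reduce missing items. Neither step says what the primary model does with a covariate that stays missing.

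**Conclusion.** The point holds in bounded form. The secondary missing-data analysis permits, but does not prescribe, adjustment for variables on the pathway from intervention to disability. If that happens, the mediated share of the effect is removed: about half or all of it in the two illustrations with mediation, none without. These figures rest on assumed values and show the mechanism, not a forecast.

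Separately, the primary rules together imply deletion of patients with an observed outcome and a missing covariate. The protocol does not say so in words; it follows from forcing in all confounders without imputation. A reader might want to put a percentage on this loss. The documents do not allow it: Figure 2 is not shown and no missingness rates are given. Up to an assumed 30% loss of practices, precision stays within the planned range. The reason to act is possible selection and the avoidable loss of randomised practices.

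**What to change.** 1. In Analysis subsets and Secondary analyses, limit covariates added to the outcome model on account of missingness to variables fixed before randomisation. Use post-randomisation predictors, including advice and bed rest, only as auxiliary variables in multilevel multiple imputation (practice as cluster) or in response weights, leaving the outcome model's covariates unchanged.
2. In Primary analyses, state that missing pre-randomisation practice and practitioner covariates are filled by simple imputation (mean, or a missing category), so that everyone with an observed outcome is analysed. Report how many values were filled, by arm.

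The cost is a few sentences and modest extra analysis. No new data are needed.
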